# Australasian Malignant PLeural Effusion (AMPLE)-3 trial: study protocol for a multi-centre randomised study comparing indwelling pleural catheter (±talc pleurodesis) versus video-assisted thoracoscopic surgery for management of malignant pleural effusion

**DOI:** 10.1186/s13063-022-06405-7

**Published:** 2022-06-27

**Keywords:** Pleural effusion, Indwelling pleural catheter, Malignant, Video-assisted thoracoscopic surgery, Randomised controlled trial

## Abstract

**Introduction:**

Malignant pleural effusions (MPEs) are common. MPE causes significant breathlessness and impairs quality of life. Indwelling pleural catheters (IPC) allow ambulatory drainage and reduce hospital days and re-intervention rates when compared to standard talc slurry pleurodesis. Daily drainage accelerates pleurodesis, and talc instillation via the IPC has been proven feasible and safe. Surgical pleurodesis via video-assisted thoracoscopic surgery (VATS) is considered a one-off intervention for MPE and is often recommended to patients who are fit for surgery. The AMPLE-3 trial is the first randomised trial to compare IPC (±talc pleurodesis) and VATS pleurodesis in those who are fit for surgery.

**Methods and analysis:**

A multi-centre, open-labelled randomised trial of patients with symptomatic MPE, expected survival of ≥ 6 months and good performance status randomised 1:1 to either IPC or VATS pleurodesis. Participant randomisation will be minimised for (i) cancer type (mesothelioma vs non-mesothelioma); (ii) previous pleurodesis (vs not); and (iii) trapped lung, if known (*vs* not). Primary outcome is the need for further ipsilateral pleural interventions over 12 months or until death, if sooner. Secondary outcomes include days in hospital, quality of life (QoL) measures, physical activity levels, safety profile, health economics, adverse events, and survival. The trial will recruit 158 participants who will be followed up for 12 months.

**Ethics and dissemination:**

Sir Charles Gairdner and Osborne Park Health Care Group (HREC) has approved the study (reference: RGS356). Results will be published in peer-reviewed journals and presented at scientific meetings.

**Discussion:**

Both IPC and VATS are commonly used procedures for MPE. The AMPLE-3 trial will provide data to help define the merits and shortcomings of these procedures and inform future clinical care algorithms.

**Trial registration:**

Australia New Zealand Clinical Trial Registry ACTRN12618001013257. Registered on 18 June 2018.

Protocol version: Version 3.00/4.02.19

**Supplementary Information:**

The online version contains supplementary material available at 10.1186/s13063-022-06405-7.

## Introduction

Malignant pleural effusion (MPE) affects over 10,000 Australians and an estimated 5 million people worldwide each year [1]. MPE can complicate most cancers, including 30% of breast and lung cancers and more than 90% of malignant pleural mesotheliomas [2]. The resultant breathlessness is disabling and significantly impairs quality of life. Key goals of management are to relieve breathlessness and enable physical activity while minimising interventions and time spent in hospital, in a cost-effective manner. MPE is associated with a major healthcare burden with annual care costs of over $5 billion in the USA alone [3].

MPE usually indicates incurable cancer with a variable prognosis from days to years; median survival can be as short as four months in lung carcinomas and 12 months in mesothelioma [4–6]. Prognosis depends on multiple factors including performance status and tumour type [4]. Younger, fitter patients, with a prognostically favourable tumour type can be expected to have a significantly longer survival than those with comorbidities and less favourable cancers and, therefore, may warrant significantly different MPE management approaches. A definitive procedure to prevent re-accumulation of effusion post-drainage is typically required to reduce repeated interventions, hospitalisations, and complications. Various treatments with definitive intent of fluid control are available but each has its advantages and limitations.

Surgical pleurodesis is viewed by many clinicians as a one-off intervention with high long-term success rates. Video-assisted thoracoscopic surgery (VATS) has replaced open thoracotomy as the preferred surgical procedure for pleurodesis [7]. If successful, VATS pleurodesis can provide lifelong freedom from the effusion and is the first-line therapy in many institutions worldwide [8]. Reported success rates of 68 to 100% are based mainly on retrospective or single-centre studies [9–12]. One retrospective review of mesothelioma found a re-intervention rate of 32% in the subgroup of patients who underwent VATS pleurodesis at a median of 30 days post-surgery, which was not significantly different from the bedside talc slurry pleurodesis subgroup [13]. Disadvantages of VATS include complications such as fever, pneumonia, and prolonged air leak, occurring in up to 28% of cases [9–12, 14–20]. Post-VATS intercostal neuralgia is also a common long-term complication affecting 25% of patients [21]. VATS pleurodesis requires a median of 5.8 to 10.3 days of hospital stay [12, 15]. The frequent need for general anaesthesia and single lung ventilation also limit the availability of the procedure to patients who are considered fitter and have longer expected survival.

The limitations of surgical pleurodesis have encouraged the development of alternative approaches. Indwelling pleural catheter (IPC) is an ambulatory drainage device for patients with MPE that can be managed on an outpatient basis. A tunnelled catheter is sited and patients (and/or their carers) are educated in home drainage. Multiple prospective studies in the past decade have firmly established IPC as a strong alternative to talc slurry pleurodesis [22, 23]. IPC offers a significant reduction in the need for further interventions for drainage of symptomatic pleural fluid. In prior trials, only 2–6% of IPC-treated patients required further pleural drainages (compared with over 20% in conventional talc pleurodesis) [9, 22, 23]. IPC is also associated with a reduction in hospital days *vs* talc slurry pleurodesis [22–24]. IPC provides effective palliation in the presence of trapped lung, a cohort in whom talc slurry pleurodesis fails due to lack of visceral and parietal pleural apposition [25, 26].

Spontaneous pleurodesis occurs in 40–51% of patients with IPC at a median of 59.0–80.5 days, allowing removal of the IPC [6, 23, 24, 27], especially if the IPC is drained aggressively (e.g., daily) [28, 29]. Talc slurry instillation via IPC has been shown to be safe and feasible with pleurodesis success rates of > 90% in two prospective case series [30, 31]. The feasibility of this combined (IPC + talc) approach was confirmed in a randomised controlled trial (RCT) [32]. Combining IPC with talc pleurodesis and daily drainage may improve outcomes. IPC has its own unique range of complications such as infection (~ 5%) [33, 34], symptomatic loculations (8–13%) [6, 27, 35], and catheter tract metastases (10%) [36]. IPC care can be time consuming and, for patients with better prognoses, may become a burden. IPC also requires ongoing consumables that may result in reduced cost-effectiveness with longer survival [37–39].

Clinical equipoise exists regarding the optimal treatment for MPE, and there is significant dichotomy worldwide. Due to a paucity of high-quality data, decisions are often based on clinician bias and available resources. VATS pleurodesis is conventionally regarded as the optimal approach to provide long-term control of MPE in patients who are fit for surgery. While the role of IPC over bedside talc slurry pleurodesis in the MPE population has been proven, RCTs of IPC (± pleurodesis) to date have investigated patients with advanced cancers, approximately one third of study patients dying within 3 months. Studies of IPC in patients with better performance status and predicted survival, who would also be suitable for VATS pleurodesis, are overdue. Whether IPC combined with talc pleurodesis, and daily drainage would be superior to VATS pleurodesis is unknown. A prospective randomised comparison is required to answer this question.

## Methods

### Study design

The Australian Malignant PLeural Effusion (AMPLE) trial-3 is a multi-centre, open-labelled, randomised (trial entry) study to determine the comparative efficacy of two frequently applied interventions for MPE (VATS or IPC) in improving patient-related clinical outcomes.

### Study setting, participant screening, selection, and recruitment

This trial will be conducted at tertiary centres across Australia, New Zealand, Canada, and the UK. Currently involved institutions are listed in the ethics section. The full list of enrolling sites will be updated regularly on the trial registration website (URL: ACTRN12618001013257). The site investigator or designated research staff will screen patients in both inpatient and outpatient settings. Consecutive eligible patients will be offered trial entry and screening logs will be kept.

Research teams at each site will be contacted regularly by the lead site to discuss hurdles to recruitment. Enrolment and screening logs, including reasons for non-inclusion, will be maintained and de-identified logs will be sent to the lead site monthly.

### Inclusion criteria

Patients with symptomatic MPE that requires definitive intervention, with a predicted survival of more than 6 months and an Eastern Cooperative Oncology Group (ECOG) performance status of 0 to 1 will be included. Patients with a performance status ≥ 2 may be included if it is felt that removal of the pleural fluid would improve their performance status to 1 or better. MPE is defined as either histocytologically proven pleural malignancy or an exudative effusion with no other cause in a patient with known primary extra-pleural malignancy.

### Exclusion criteria

Exclusion criteria includes age < 18 years; unfit to undergo surgical procedure (American Society of Anaesthesiology Score ≥ 4); significant loculations likely to preclude effective drainage via IPC; pleural infection; chylothorax; pregnancy or lactation; uncorrectable bleeding diathesis; and previous ipsilateral lobectomy/pneumonectomy and inability to consent or comply with the protocol.

### Informed consent

Potential participants will be provided with verbal information and the participant information and consent form (PICF) to read by a member of the research team. They will be given time to ask questions and to discuss the study with family/carers and their GP.

### Interventions

#### VATS arm

Participants randomised to the VATS arm will undergo surgery within two weeks of randomisation. VATS is usually performed in an operating theatre, using either general anaesthesia or sedation. The pleural fluid will be removed, and adhesions can be divided. Assessment of lung re-expansion will be performed intra-operatively. If lung re-expansion is adequate (as judged by the operating surgeon), a variety of techniques may be employed to induce pleurodesis, including, but not limited to, talc poudrage and mechanical abrasion. Decortication may be performed if deemed appropriate and feasible. A chest drain (non-IPC) will be left in situ after the surgery. Post-operative care will be performed as per local practice.

#### IPC arm

IPCs will be inserted as per local protocols. If full lung expansion (see Trapped Lung SOP, Additional file 1) is achieved after drainage of the effusion (typically assessed 1 day post-insertion), sterile talc (4–5 g, graded) will be instilled as a slurry via the IPC, and subsequent management (e.g., use of suction) will follow local protocols for talc slurry pleurodesis at each site. Daily drainage with suction bottles will then be performed for 7 to 10 days after talc instillation until outpatient review. Successful development of pleurodesis is defined as fluid output of less than 50 ml on three consecutive drainage attempts via IPC without evidence of fluid accumulation on imaging. The IPC can be removed when pleurodesis is achieved. In the case of ongoing pleural fluid production and drainage via the IPC, daily drainage can continue or be adjusted to a symptom-guided drainage regimen as determined by the treating team.

If the lung does not fully expand following complete evacuation of pleural fluid (see Trapped Lung SOP, Additional file 1), the participant will be discharged on a daily drainage regimen to allow the best chance of full lung re-expansion, which will be assessed at outpatient follow-up. In the event of full lung expansion (≥ 75% pleural apposition) in association with ongoing fluid production, talc instillation via IPC can be considered (as described above) and followed by daily drainage and review at 7–10 days after the attempted pleurodesis. If the lung remains trapped, further drainage will follow a symptom-guided drainage regimen. At any time, if the output is < 50 ml/drainage on three consecutive drainage attempts at least 24 hapart, with no evidence of symptomatic fluid accumulation, the IPC can be removed.

### Standard care and follow-up

Participants in both arms will be managed by their own clinical teams and receive all other usual medical treatment (including chemotherapy and radiotherapy). All participants and carers will have access to the research team should any concerns arise. This cohort will remain under the continued care of a physician or thoracic surgeon following trial completion.

Participants are advised prior to enrolment that they are free to withdraw from the trial at any time if they so wish. Following randomisation, changes to the intervention plan may be made at the discretion of the treating physician or due to participant request.

### Strategies to improve adherence to interventions and participant retention

Potential participants, as part of the informed consent process, will have the study procedures and visit plan discussed in detail. An emphasis will be placed on the need for attendance at all study visits. Where participants do not attend planned study visits, the research team will make contact and book an unscheduled visit if required.

### Outcomes

Data will be collected by the site investigators from the participant at follow-up visits (see 16) and from their hospital record.

#### Primary endpoint

The primary outcome is the need for an ipsilateral pleural intervention within 12 months of randomisation for symptomatic recurrence of pleural effusion. Pleural intervention will be defined as an ipsilateral surgical procedure, chest drain insertion or thoracentesis with therapeutic intent.

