#### Secondary endpoints

Repeat ipsilateral pleural intervention including diagnostic aspiration, e.g., for the investigation of possible infection will be identified as aboveTime to symptomatic effusion recurrence will be measured from the date of procedure, by performing radiological investigations if the participant describes worsening dyspnoea at a study visit. Recurrent effusion is defined as greater than 25% increase in opacification on chest x-ray (CXR) on the side of the intervention, and evidence of pleural fluid on ultrasoundAll-cause and pleural-related hospital days will be measured. Length of stay post-procedure and hospitalisation for any cause (except for elective admissions for chemotherapy) will be recorded for all participants post-enrolment until the end of follow-up period or death. Admissions will be analysed as total admission days (and number of episodes) and as pleural-related admission daysDegree of breathlessness will be measured using a 100-mm visual analogue scale (VAS), which is a validated score of dyspnoea in MPE [23]. The VAS is a 100 mm line anchored with “no breathlessness” at 0 mm and “worst breathlessness imaginable” at 100 mm and will be done during the aforementioned outpatient reviews. Two independent researchers will measure all VAS scores and the mean score will be calculated. Differences in scores of more than 3 mm in both measurements will be repeated by the same observersPain will be assessed using a 100-mm VAS with timing and measurement as for breathlessnessQuality of Life (QoL) will be measured using two instruments, the EQ-5D-5L questionnaire and VAS QoL, both employed as primary or secondary end-points in previous RCTs [23, 40]. VAS QoL records self-rated quality of life on a 100 mm line, anchored with “best imaginable quality of life” at one end-point and “worst imaginable quality of life” at the other. QoL will be measured at each study visitPhysical activity patterns will be evaluated by a well-validated triaxial accelerometer (ActiGraph GT3X+, Pensacola, FL, USA) providing an indication of functional status [41]. Standard data processing will be applied and the weekly duration of low, moderate, and vigorous-intensity physical activity determined in accordance with established ranges. This will be performed at the lead-site onlyAdverse events will be recorded from time of enrolment until end of follow-up or death. An adverse event is defined as any complication associated with the IPC or VATS pleurodesis, including, but not limited to, pleural infection, cellulitis, pain, symptomatic loculation +/− requirement of intrapleural fibrinolytics, tube blockage, catheter tract metastases, parenchymal air leak, etc., and any peri/post-procedural complications such as prolonged air-leak, atelectasis, pneumonia, cardiovascular complications, acute kidney injury, or drop in haemoglobin requiring transfusionEconomic analysis will be performed by obtaining inpatient costs from the hospital. Outpatient pleural care costs and equipment utilisation will be noted (Western Australia only)Overall survival will be recorded from date of enrolment to death or end of study follow-up

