### Sample size

This study will enrol 158 patients to detect a 5% reintervention rate in optimised IPC vs 25% reintervention rate in VATS (based on previous studies [13, 22, 23]). The sample size calculation was carried out using an anticipated Fishers exact test to compare these proportions in each of the two groups. With a 5% significance level and a power of approximately 90%, we would need 75 patients per group with an additional 4 patients per group to allow for dropouts (5% anticipated) giving a total of 158 patients. Withdrawal or loss to follow-up only occurred in 4.8% (7/146) patients in our previous AMPLE-1 trial of MPE [22].

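### The primary endpoint omits fibrinolytics given through a catheter already in place, an asymmetry that favours IPC by an amount the protocol does not allow one to fix

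*Protocol article*

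**What the plan says.** The Primary endpoint section sets the outcome as the "need for an ipsilateral pleural intervention within 12 months of randomisation for symptomatic recurrence of pleural effusion" and then lists what qualifies: "Pleural intervention will be defined as an ipsilateral surgical procedure, chest drain insertion or thoracentesis with therapeutic intent". The list is closed.

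The Secondary endpoints section places "symptomatic loculation +/− requirement of intrapleural fibrinolytics" among the adverse events. The wider re-intervention endpoint in the same section names diagnostic aspiration as an addition, but not fibrinolytics.

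In the Introduction, loculation is one of the recognised IPC complications: "symptomatic loculations (8–13"%). The same section says that in prior trials "only 2–6% of IPC-treated patients required further pleural drainages". The Sample size section plans to "detect a 5% reintervention rate in optimised IPC vs 25% reintervention rate in VATS".

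Under the VATS arm section, participants leave theatre with an ordinary chest drain, not an IPC. Under the IPC arm section the catheter stays until pleurodesis: "In the case of ongoing pleural fluid production and drainage via the IPC, daily drainage can continue", or the regimen may become symptom-guided.

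**The concern.** The same clinical problem can be scored differently by arm. A VATS participant whose symptomatic fluid returns would normally need a tap, a drain or an operation, and each is a primary event. An IPC participant with symptomatic loculated fluid may be treated with fibrinolytics through the tube already there, and that is not an event.

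The cited loculation rate is larger than the event rate assumed for the IPC arm, so the omitted treatments could be of the same order as the counted ones. The Discussion promises guidance on which treatment is best for patients suited to both. In an open-label trial, a lower re-intervention rate with IPC could partly reflect which treatments are counted.

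**Working it through.** **Step 1. The plan's own figure.** Inputs from the Sample size section: 5% vs 25%, 5% significance level (taken as two-sided), about 90% power, Fisher's exact test, 5% dropout.

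Uncorrected: n = [1.960·√(2·0.15·0.85) + 1.282·√(0.05·0.95 + 0.25·0.75)]² / 0.20² = 64.9, so 65 per group.

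With continuity correction: n' = (64.9/4)·[1 + √(1 + 4/(64.9·0.20))]² = 74.5, so 75 per group. Dropout: 75/0.95 = 78.9, so 79 per group and 158 in total.

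The stated figures reproduce. Exact two-sided Fisher power at 75 per group is 92.8%, compatible with the stated level of about 90%.

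**Step 2. Loculation against the assumed event rate.** 8/5 = 1.6 and 13/5 = 2.6. In 75 IPC participants, 5% is 3.75 events, while 8–13% is 6 to 9.75 participants with symptomatic loculation. The second figure is a rate of loculation, not of uncounted treatment.

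**Step 3. Uncounted treatment.** Let f be the share of symptomatic loculations treated with fibrinolytics alone. The protocol does not give f, so it is an assumption here. Uncounted events = f × (8–13%). If none of them overlaps the 5%, the IPC rate in an analysis that counts them is 5% + f × (8–13%). The last column is exact two-sided Fisher power for that supportive analysis at 75 per group, with VATS held at 25%.

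| f | Points added | IPC rate | Difference from 25% | Power |
|---|---|---|---|---|
| 0 | 0 | 5% | 20 points | 93% |
| 0.25 | 2–3.25 | 7–8.25% | 18–16.75 points | 83–74% |
| 0.5 | 4–6.5 | 9–11.5% | 16–13.5 points | 69–49% |
| 1 | 8–13 | 13–18% | 12–7 points | 39–13% |

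**Step 4. When the uncounted rate would exceed 5%.** This needs f above 5/8 = 62.5% at 8% loculation, or above 5/13 = 38.5% at 13%. Only part of the plausible range of f meets this.

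**Step 5. What the table does not describe.** The primary definition is kept, so the planned power of the primary analysis does not move. Holding VATS at 25% is also an assumption, because fibrinolytics could be given early through the post-operative drain, and the supportive analysis would count those too.

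**The case against.** The strongest reply is that the endpoint is explicit and fits the trial's purpose. The Introduction names fewer interventions as a goal of care, and avoiding new procedures is the benefit claimed for IPC. The 5% assumption lies within the 2–6% quoted for further drainages, so the endpoint and the planning figure describe similar events. This stands, and it is why the primary definition should be kept. Continued drainage through the IPC is the assigned treatment and is not a missed event.

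A reader might infer that the definition favours IPC by more than its whole assumed event rate. The documents do not support that. The adverse event wording shows that not every loculation receives fibrinolytics, and no rate of use is given. Cases that go on to a tap, drain or operation for symptomatic recurrence already count and may sit inside the 5%. The 8–13% comes from earlier studies, while this trial excludes significant loculations at entry and uses talc with daily drainage where the lung expands, so its rate could differ either way.

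A reader might also infer that the trial cannot show which option controls the effusion better. That goes too far: time to symptomatic recurrence is a secondary endpoint with one radiological and ultrasound definition for both arms, and breathlessness and pleural-related hospital days are also measured. These soften the concern but do not correct the re-intervention comparison itself.

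Sensitivity analyses are commonly left to an SAP, and none is shown here, so the absence of one is not the point. The point is the closed event list, which the protocol itself fixes.

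**Conclusion.** The gap and its direction follow from the text: fibrinolytics through an existing IPC for symptomatic loculated fluid are not primary events, while the usual remedies after VATS are. The size is not known. By the figure from earlier studies, 8–13% is a ceiling on the IPC participants affected, against an assumed 5% event rate. The uncounted part is 2–3.25 points if a quarter are treated with fibrinolytics alone, 4–6.5 if half are, and 8–13 only if all are. This assumes that the earlier loculation rate carries over and that none of these cases is already within the 5%.

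The trial is not shown to be underpowered for its stated primary analysis. What is affected is how far a positive result can be read beyond new invasive procedures.

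**What to change.** Keep the primary definition, since recruitment began in 2019. Before comparative results are seen, including those of the interim analysis at 60–80 participants, add the following to the analysis plan:

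- One sensitivity analysis of the primary outcome, applied identically in both arms, that also counts intrapleural fibrinolytic instillation for symptomatic fluid.
- Beside it, the proportion in each arm alive at 12 months with a catheter still in place.
- A rule that, if the two analyses disagree, the conclusion is worded as fewer new invasive pleural procedures. Disagreement is best judged on the estimated difference and its confidence interval, since loss of significance alone could reflect the lower power of the supportive analysis.

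The cost is plan wording. Fibrinolytic use falls within the adverse events already collected, and Table 1 schedules adverse event review and, in the IPC arm, assessment for pleurodesis through month 12. Neither treatment, sample size nor the primary test changes. The downside is that the supportive result may be less favourable to IPC and, at 75 per group, has less power than the primary analysis.
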